##### Qualitative Study

Conventional content analysis [26] will be used to analyze the transcribed interviews, and coding will be performed using NVivo software (QSR International). A conventional inductive approach will first be used to gain direct information from study participants, without imposing preconceived categories or theoretical perspectives, and to ensure that knowledge generated from the content analysis is based on the participants’ unique perspectives [27]. After themes have been derived through inductive content analysis, a deductive approach will be used as the final step to frame and structure the findings [26]. Therefore, the themes generated through inductive content analysis will be delineated and mapped in accordance with Chaudoir’s multilevel framework for the assessment of factors affecting the implementation of health innovations [28].

## Results

Patient recruitment began in January 2019 at PMCC, UHN, Toronto. The study is currently in progress, and a total of 76 participants have been recruited as of February 24, 2020 (39 in the intervention group and 37 in the control group). The final analysis is expected to be completed by the winter of 2021. This study will be among the first to substantiate the implementation of remote titration facilitated by telemonitoring and its impact on patient health outcomes.

## Discussion

### Principal Results

This study aims to determine how the combination of remote titration and telemonitoring affects GDMT optimization compared with the standard of care. Specifically, the objectives of this study are to assess the effectiveness and implementation of remote titration facilitated by telemonitoring. Telemonitoring is a potential component in the management of HF that allows patients to remotely provide reliable and real-time physiological data for clinical decision support. Studies have demonstrated that the use of telemonitoring in the HF population is associated with a reduction in hospitalizations and readmissions and improved mortality [29-32]. Patient and clinician perceptions are positive, and telemonitoring is viewed as a useful and efficacious tool that can be used to promote positive outcomes in the HF population [33-35].

Despite this, only a few trials have attempted to use telemonitoring for the purpose of remote titration of HF medication. A study conducted by D’Onofrio et al [36] and Palmisano et al [37] assessed the effectiveness of a structured program for BBL titration and found that remote titration allowed 76% of patients in the intervention group to achieve target doses compared with only 38% of patients in the control group. Similarly, Spaeder et al [38] also performed a study that focused on rapid titration of the BBL carvedilol and compared in-office titration with a combined in-office and remote titration model. The study found no statistical difference in the proportion of patients who reached the target doses. However, the time frame required to reach the final dose was significantly shorter in the intervention group (mean 33.6, SD 16.6) than in the control group (mean 63.7, SD 20.2).

Of note, a few other studies that have attempted to perform remote medication titration did not contain any telemonitoring components, such as a smartphone-based app or a web platform. Instead, patients periodically called or were contacted by a clinician and relayed their measurements and symptom data over the phone. Two such trials by Steckler et al [39] and Moyer-Knox et al [40] assessed BBL titration over the phone. Steckler et al [39] found that the proportion of patients receiving BBLs at any dose increased from 61% at baseline to 97% after optimization, and the proportion of patients receiving target BBL doses increased from 12.5% at baseline to 40.6% after optimization. Moyer-Knox et al [40] found that 96% of patients reached therapeutic doses (6.25 mg twice daily) and 71% of patients reached target doses of 25 mg twice daily within approximately 8 weeks.

These trials provided preliminary evidence demonstrating that remote titration (with or without the aid of telemonitoring) of BBLs can be successful and results in a higher proportion of patients reaching target doses within shorter time frames.

### Strengths and Limitations of the Study

Unlike previous studies that focused solely on the titration of BBLs, a strength of this study is that it encompasses the titration of full triple therapy for patients with HF. In addition, the mixed methods design of this study will allow triangulation of data from quantitative and qualitative assessments, thereby enhancing data validity. Methodological triangulation enables the validation of findings through the collection of data from multiple sources and via different methods. Specifically, data from interviews with clinicians and patients will be used to complement, confirm, and explain the results of the quantitative study. Furthermore, the previously existing evidence regarding remote titration and the currently available data on the effectiveness of Medly telemonitoring for patients with HF [22,23,33,41] make it possible to adopt an effectiveness-implementation hybrid design [17]. Therefore, implementation-related questions can be explored much earlier than could be achieved in separate sequential intervention and implementation study designs [17].

A limitation of this study is its single-center nature and the availability of dedicated specialized staff to support the intervention. The patient population enrolled in this study was recruited from a single specialized heart function clinic. The PMCC Heart Function Clinic has implemented telemonitoring as a standard of care. The Medly Program was launched at the clinic in 2016, and cardiologists are familiar with monitoring patients through Medly. The familiarity of the clinicians involved in this study with telemonitoring as well as the existing processes for alert management and communication of information obtained through the Medly system may contribute to the mitigation of challenges that could otherwise be encountered. Furthermore, the intervention is supported by a dedicated nurse coordinator. As access to multidisciplinary HF services varies between clinics, additional staffing limits the potential generalizability and external validity of the study. Finally, as our study investigates changes in the process of care, blinding could not be applied to clinicians. However, patient randomization is performed using sealed opaque envelopes containing randomly generated treatment allocations. Patients in the intervention group follow a structured predetermined remote titration schedule, whereas patients in the control group continue to be treated as per the standard of care by their respective cardiologists. Thus, the lack of clinician blinding is not expected to have an impact on the outcomes of the study.

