### Study Protocol

#### Participant Enrollment and Randomization

##### RCT

Study participants are recruited from the PMCC Heart Function Clinic. Eligible participants are first identified by the cardiologist. During their usual visit to the Heart Function Clinic, all patients who meet the study’s inclusion and exclusion criteria (listed in Textboxes 1 and 2, respectively), are told about the study and asked by a member of their circle of care if they are willing to speak to the nurse coordinator regarding participation. Patients who agree meet with the coordinator immediately after their visit with the cardiologist, and a written informed consent is obtained from each patient. Patients are then randomized 1:1 into control and intervention groups. A web-based computer-generated randomization tool is used to perform block randomization in blocks of 4. The generated sequence is used to create randomization envelopes, and the nurse coordinator is provided with randomly generated treatment allocations within sealed opaque envelopes. Following enrollment, the envelopes are used to determine if the patient is in the intervention or control group. Cardiologists are notified into which group their patients are randomized.

Patient inclusion criteria.Able to provide informed consent to participate in the program18 years or olderDiagnosed as having heart failure (HF) and followed up by a cardiologist at the Peter Munk Cardiac Centre Heart Function Clinic, who has the primary responsibility for management of the patient’s HFNew York Heart Association Classes I to IIIStable HF defined as no hospitalization within 1 monthPatient is not yet at target doses of guideline-directed medical therapy (angiotensin-converting-enzyme inhibitor, and/or angiotensin receptor blocker, and/or beta blocker, and/or angiotensin receptor-neprilysin inhibitors, and/or mineralocorticoid receptor antagonist at suboptimal doses), and hence qualifies for up-titrationPatient or their informal caregiver speaks and reads English adequately to participate in the program and understand the alerts or prompts in the Medly applicationAbility to comply with using Medly (eg, able to stand on the weight scale, able to answer symptom questions)

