#### Intervention Versus Control Groups

The recommended therapeutic approach for patients with HF and reduced left ventricular ejection fraction (LVEF<40%) consists of triple therapy with either an ACEI or ARB or ARNI, BBL, and MRA, titrated to target doses [10]. However, these doses are not often achieved in clinical practice [7]. Patients identified as receiving suboptimal doses of HF medications are enrolled and randomized at a ratio of 1:1 to 1 of 2 treatment groups:

Control group—standard titration management strategy consisting of regular in-office visits.Intervention group—remote titration management strategy consisting of telephone contacts facilitated by data from the Medly system and in-office visits as deemed necessary by the patient’s care team.

Both groups are titrated in accordance with the recommendations of the HF management guidelines. Participants in the intervention group, as per Medly standard of care, are asked to take daily weight and blood pressure readings and answer questions on symptoms. Patients are also provided with requisitions for blood work to be performed at local laboratories when requested. Titration checkpoints are scheduled biweekly unless specified otherwise by cardiologists. Patients are contacted by phone, and medication changes are performed during these calls based on data obtained through Medly and the latest blood work. Patients in the intervention group still visit the hospital for follow-ups at their cardiologist’s discretion and to perform echocardiograms, electrocardiograms (ECGs), and cardiopulmonary exercise testing (CPET).

Participants in the control group attend regular visits and are provided with the current standard of care. As the Medly system is integrated into the PMCC Heart Function Clinic as part of the standard of care, patients in the control group are also monitored through Medly. However, no remote titrations occur, and medication changes are performed during clinic visits. At the clinic visit, patients have their measurements taken, such as their blood pressure, weight, and heart rate. The clinicians inquire about their symptoms, diet, exercise, and adherence to medication. Blood tests, echocardiograms, ECGs, and CPETs are performed as required. Medication changes are performed based on the data collected through these assessments.

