The titration process is terminated when patients reach target doses or maximum tolerated doses. A follow-up clinic appointment is scheduled within 3 months of titration completion, as per the standard of care. Throughout this process, the importance of patients’ adherence to program requirements in terms of daily measurements and symptom reporting is emphasized and strictly monitored to ensure prompt identification of potential changes in their condition.

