#### Data Collection

##### RCT

The primary outcome measures will be the proportion of patients who achieve target doses and the time to dose optimization. Additional measures will include patient health outcomes (including, but not limited to, New York Heart Association [NYHA] class, LVEF, and brain natriuretic peptide [BNP] levels), the number of visits and/or calls required to achieve target doses, and health care resource utilization.

Information will be obtained by reviewing the patients’ electronic patient record (EPR) charts and Medly data and documentation throughout the study by the study coordinator. Baseline and poststudy medications and dosages for each patient and baseline and poststudy clinical measures, including NYHA class, LVEF, and BNP levels, will be determined through manual EPR chart reviews. Health care utilization will primarily be determined through EPR chart reviews. However, this information will be supplemented through patient self-reporting to account for situations in which patients use services outside of UHN. Data regarding the titration process, such as the number of visits and/or phone calls performed, actions undertaken, and any adverse events that occurred throughout the study, will be documented by the study coordinator. The number of visits, phone calls, and total contact points will be recorded in detail for each group to determine the impact of remote titration on the GDMT optimization process.

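### The reasons given for expecting no effect of unblinded clinicians do not support that claim, because both primary outcomes follow from those clinicians' dosing and stopping decisions

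*Protocol article*

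**What the plan says.** All references are to the protocol article.

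- **Strengths and Limitations of the Study** concedes that clinicians are unblinded and gives three reasons for setting this aside. The first is concealment: "patient randomization is performed using sealed opaque envelopes containing randomly generated treatment allocations". The second concerns the intervention arm: "Patients in the intervention group follow a structured predetermined remote titration schedule". The third concerns the control arm: "patients in the control group continue to be treated as per the standard of care by their respective cardiologists". It then concludes: "Thus, the lack of clinician blinding is not expected to have an impact on the outcomes of the study".
- **Participant Enrollment and Randomization (RCT):** "Cardiologists are notified into which group their patients are randomized".
- **Intervention Versus Control Groups:** "Titration checkpoints are scheduled biweekly unless specified otherwise by cardiologists". In-office visits in that arm are left to the care team. Dose changes are made in phone calls in the intervention arm and at clinic visits in the control arm. The end of titration is defined for both arms: "The titration process is terminated when patients reach target doses or maximum tolerated doses".
- **Data Collection (RCT):** "The primary outcome measures will be the proportion of patients who achieve target doses and the time to dose optimization".
- **Sample Size Calculation** adopts the proportion achieving target doses as the new primary outcome. It supports this with pilot counts of patients who completed titration within 6 months: 18 of 21 (86%) versus 10 of 21 (48%).

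**The concern.** Concealment of allocation and blinding after allocation are separate safeguards, and the article uses the first to dismiss the absence of the second. Once the envelope is opened, the people who raise, hold or stop doses know the arm.

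The outcomes are not remote from those decisions. Time to dose optimization ends when titration is judged finished. Attainment of target dose depends on the decision to keep going. Stopping at maximum tolerated dose is a judgement, and the article describes neither a criterion nor a separate assessor for it.

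Two things are at stake. A reader is told the design has a protection that its stated features do not provide. And if judged stops are counted as success, a difference in judgement between arms could pass for a difference in dosing.

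**Working it through.** **1. Does each reason support the conclusion?**

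- *Envelopes.* They prevent foreknowledge of the next assignment. They have no bearing on conduct afterwards, and the enrollment section says cardiologists are told the arm.
- *Predetermined schedule.* Contacts are biweekly by default, with a cardiologist override. Even a rigid schedule fixes when a patient is contacted, not whether a dose is raised or titration is ended.
- *Control care by their own cardiologists.* Those cardiologists know the arm, so this describes a route for performance bias rather than a barrier to it.

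**2. Who decides that titration is over?** No sentence says. The treating team makes the dose changes in both arms and no other assessor is described, so the inference is that the same unblinded team decides.

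**3. Which outcome is affected?**

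- Time to dose optimization: directly, through the date at which titration is taken as finished.
- Proportion outcome, read strictly as target dose: a stop below target is a failure, so calling it maximum tolerated cannot inflate success. Only unequal effort at up-titration remains.
- Proportion outcome, read as completed titration: a stop at maximum tolerated dose is a success, so judgement enters the count. The pilot rates may have been built this way, since the stopping rule allows either end.

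**4. The plan's own figure.** Inputs from Sample Size Calculation: 45% v 75%, power 80%, two-sided alpha .025. The arcsine formula is n = 2(z₀.₉₈₇₅ + z₀.₈₀)² / h², with h = 2·arcsin√0.75 − 2·arcsin√0.45 = 0.6238. This gives 2(2.2414 + 0.8416)² / 0.6238² = 48.86, so 49 per group, as stated. With 10% added, 49 × 1.10 = 53.9, so 54. The sample size is not in dispute; 49 per arm is used below.

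**5. Illustration under the completed-titration reading.** Assume no true effect and a true rate of 10/21 = 0.4762 in both arms. A share q of intervention non-completers, and a share r of control non-completers, is declared complete. The apparent rates are 0.4762 + q × 0.5238 and 0.4762 + r × 0.5238. For example, q = 0.20 gives 0.4762 + 0.1048 = 0.5810. The rejection probability is the sum, over all pairs of counts from two binomials with 49 per arm, of the pairs where the uncorrected chi-square test is significant at two-sided .025.

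| q (intervention) | r (control) | Apparent rates | False positives |
|---|---|---|---|
| 0 | 0 | 47.6% v 47.6% | 2.2% |
| 5% | 0 | 50.2% v 47.6% | 2.6% |
| 10% | 0 | 52.9% v 47.6% | 4.0% |
| 20% | 0 | 58.1% v 47.6% | 10.6% |
| 30% | 0 | 63.3% v 47.6% | 24.2% |
| 20% | 10% | 58.1% v 52.9% | 4.3% |
| 30% | 15% | 63.3% v 55.5% | 7.6% |

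The documents give no value for q or r; both are assumptions. With 54 per arm the five one-sided rows become 2.6%, 3.2%, 5.0%, 12.9% and 27.9%.

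**The case against.** The strongest case on the other side has five parts.

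- **Blinding is infeasible, and clinicians' titration behaviour is part of the strategy being compared.** This stands. The lack of blinding is not the fault; the statement that no effect is expected is.
- **The primary outcome is worded as target doses.** This stands and limits the point. A reader might infer that the primary proportion is simply a subjective end point that unblinded staff can inflate. The documents do not establish that. It holds only if completed titration is what will be counted, and the article is ambiguous between the two.
- **The wording is cautious.** The article says no impact is expected, not that none is possible. This is correct, but the stated reasons do not support the softer claim either.
- **A default schedule with exceptions can fairly be called structured.** This largely stands. A reader might conclude that the schedule is not predetermined at all. The text shows loose wording that needs reconciling, rather than a flat contradiction.
- **The larger error rates come from one-sided shares chosen without data.** This stands. Small shares, or shares present in both arms, move the error rate little. The 47.6% base is also itself a completion rate, so it may already contain stops at maximum tolerated dose.

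A reader might also infer that the trial has no protection against this bias. That cannot be concluded from a condensed article whose full protocol and analysis plan are not shown. What can be judged is the reasoning in print, and no unseen document would make that reasoning valid.

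**Conclusion.** The point holds as a fault in a stated inference. The article's conclusion about clinician blinding does not follow from its reasons, and its own account of enrollment, checkpoints and stopping works against it. The consequence is direct for time to dose optimization. For the proportion outcome it is conditional on counting stops at maximum tolerated dose as success.

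Under that condition, the size ranges from negligible (5% in one arm) to about ten times the nominal level (30% in one arm, none in the other). It rests on assumed shares, on no true effect, and on the inference that the treating team makes the call. This should be corrected, but it does not show that the trial's result will be biased.

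**What to change.** 1. Replace the concluding sentence in Strengths and Limitations of the Study with a stated limitation: clinicians know the arm, so performance and judgement bias are possible in both primary outcomes.
2. Reconcile the description of the schedule as predetermined with the cardiologist override under Intervention Versus Control Groups.
3. Derive the proportion outcome from the medications and dosages already collected by chart review, compared with target doses specified in advance.
4. Report stopping at maximum tolerated dose as a separate category by arm, with one sensitivity analysis counting it as success in both arms. A further analysis counting it as failure would only repeat the main one.

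The cost is some rewording, one extra table and one extra analysis. The target-dose rate may come out lower than the completion rate, so it may not match the pilot percentages used for planning. No change to treatment or visit procedures is needed.

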### Significance of the Research

The significant gap that still exists in adherence to guideline-recommended evidence-based therapies for HF emphasizes the need for novel approaches to the problem of medication titration. An intervention that can successfully promote optimal GDMT use in clinical practice may substantially improve clinical outcomes in patients and reduce the burden of HF on the health care system as a whole. Although information and research on remote titration of HF medication are somewhat limited, the results of previously conducted studies have been fairly positive, pointing to a favorable impact on titration rates and timelines. This study will be among the first to explore whether remote titration facilitated by telemonitoring may be able to promote optimal GDMT use. In addition, it will be the first study to provide insight on the implementation process as well as the perception of the intervention by both clinicians and patients.

## Abbreviations

ACEI: angiotensin-converting enzyme inhibitor
ARB: angiotensin receptor blocker
ARNI: angiotensin receptor-neprilysin inhibitor
BBL: beta blockers
BNP: brain natriuretic peptide
CPET: cardiopulmonary exercise testing
ECG: electrocardiogram
EPR: electronic patient record
GDMT: guideline- directed medical therapy
HF: heart failure
LVEF: left ventricular ejection fraction
MRA: mineralocorticoid receptor antagonist
NYHA: New York Heart Association
PMCC: Peter Munk Cardiac Centre
RCT: randomized controlled trial
UHN: University Health Network
